### Randomisation

Complete randomisation will be achieved using the free software program RANDOM.ORG [57]. The first author will use the program to allocate participants to the inclusion group or the control group randomly. The study will be blinded to the care providers and data collectors, including the external data collector who will perform the outcome assessors and the statistician (investigator). A code will be allocated to each patient and not revealed before the analysis has been completed. Once the analysis has been completed, the group to which participants had been allocated will be revealed. Due to the nature of this study, where the participants will be aware whether they will have access to the educational video, it is not possible to achieve blinding for the participants.

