## Methods

### Study design

This study is designed as an experimental single-centred, two-arm parallel group randomised controlled trial over 11 months with a 1:1 allocation ratio.

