### Study setting

The study will be conducted at a regional hospital in a rural part of Northern Norway. Participants will be recruited from 3 surgical departments: the orthopaedic department, the urology and vascular/thoracic surgery department and the gastro, gynaecological, breast and surgical endocrine department. The hospital serves a broad range of mental and somatic healthcare and substance abuse patients from 20 municipalities in the region. The annual budget of the hospital is approximately 5 billion Norwegian kroner. The number of employees is about 4800. Due to logistical reasons affecting the project, which will be carried out in a rural area, patients eligible for inclusion in the study must live in 1 of 9 predetermined municipalities closest to the hospital and the location of the research team. The 9 chosen municipalities have between 1000 and 53,000 inhabitants. The Norwegian healthcare system (both primary and secondary) is publicly funded and ensures all residents with free access to care.

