### Sample size

We base our calculation of the sample size on the effect estimates of the primary outcome of the combined physical scale from the feasibility study, as estimates were not available in the literature [53]. Alpha was set at 0.05, and the beta was set at 0.20. The estimated effect size was calculated to be 7 points on a scale ranging from 0 to 100, and the standard deviation of the population outcome was 18. The patients will be distributed with 50% in the control and intervention groups. Using the sample size-means calculator [56], the necessary sample size was calculated to be 104 in each of the 2 groups. Based on the feasibility study [53], we estimated a drop-out rate of 32%. Therefore, we need to recruit 138 participants for each group.

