### Data management and monitoring

#### Data analysis

For statistical analysis, SPSS version 28.01 (IBM Corp., Armonk, NY, USA) will be used. The statistical analysis plan will be based on the principles of the intention-to-treat approach. All ratio–interval scaled data will be tested for distribution using the *F*-test. When normally distributed, parametric statistical methods will be applied, such as Student’s *t*-test and the one-way analysis of variance (ANOVA). The data will be presented through means, standard deviation (SD) and 95% confidence limits. Normal or ordinal data will be presented as absolute numbers and frequencies. Differences will be determined using non-parametric tests (e.g. the *X*^2^-test, Mann–Whitney test and rank-sum test). The data from the RAND 36 questionnaire will be decoded using the SF-36 ordinal subscales and will be transformed into a ratio scale using the syntax SF-36 manual. The results will be presented from each of the eight subscales and the two main scales. The reliability of the SF-36 scales will be calculated using Cronbach’s alpha. When the data analysis is complete, the code regarding participants’ allocation to either the intervention or control groups will be revealed. Data will be collected as long as patients are included in the study. If patients withdraw their consent, data collection will stop. Deviation from the protocol will be registered and reported accordingly. Concerning post-assignment attrition, we will conduct an attrition analysis based on variables such as the participants’ gender, age, education level, marital status and help from home care. The attrition analysis will thus reveal any systematic loss at follow-up and identify whether there are participants with a higher likelihood of attrition.

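### Department is used neither in the allocation nor in the named analysis, which costs a modest amount of precision and credibility but not validity

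*Protocol article*

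**What the plan says.** Under Study design the trial is a "two-arm parallel group randomised controlled trial over 11 months with a 1:1 allocation ratio", and under Sample size "The patients will be distributed with 50% in the control and intervention groups". The Randomisation section gives the method: "Complete randomisation will be achieved using the free software program RANDOM.ORG". In plain usage this is unrestricted allocation, and no block, stratum or minimisation factor appears anywhere in the article.

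Under Study setting, "Participants will be recruited from 3 surgical departments": orthopaedic; urology with vascular/thoracic; and gastro, gynaecological, breast and endocrine surgery. Neither the expected number of patients per department nor the spread of RAND 36 scores between departments is given.

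Under Data analysis, for normally distributed data, "parametric statistical methods will be applied", with Student's t-test and one-way ANOVA as the examples. No covariate is named.

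The first author obtains consent and assigns groups (Participants and recruitment strategy), runs the randomisation program (Randomisation) and sends each participant in the intervention group the video link (Intervention).

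**The concern.** The article itself gives reason to expect that type of surgery matters. Its Introduction says that the metabolic response can last from hours to months depending on invasiveness, anaesthesia and complications. It also says that hip fracture patients may remain hypercatabolic for up to 3 months, which is the follow-up time here. The sample size rests on the combined physical scale, which reflects mainly physical functioning, bodily pain and physical role limitations. Department is a readily available marker of type of surgery.

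If department predicts the 3-month score, two things follow from leaving it out. Variance between departments stays in the error term, and a chance excess of one department in one arm shifts the unadjusted difference. A reader of the trial report could then ask whether the result reflects the video or the case mix. A later analysis plan can add a covariate, but it cannot restore balance once patients have been allocated.

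**Working it through.** **Inputs from the Sample size section.** Difference 7, SD 18, alpha 0.05, power 80%, 104 evaluable per arm, drop-out 32%, 138 recruited per arm (276 in all). Sidedness is not stated; two-sided reproduces the plan's figure. With 32% drop-out, 138 × 0.68 = 93.8, or about 94 completers per arm (188 in all).

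**1. The plan's own figure.** n per arm = 2 × (1.960 + 0.842)² × 18² / 7² = 103.8, rounded up to 104. This agrees. By the same normal approximation, power is 80.1% at 104 per arm and 76.0% at 94 per arm.

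**2. Cost of unequal arms.** Arm size follows Binomial(N, 0.5), and the standard error is 18 × √(1/n₁ + 1/n₂).

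- At 276 randomised, the 95% limits for an arm are 122 and 154. An exact 138:138 split has probability 4.8%, a difference of 20 or more has probability 25%, and a 60:40 or worse split about 0.1%.

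| Evaluable | Power, equal arms | Power, average under simple randomisation | Power at the 95% limit |
|---|---|---|---|
| 208 | 80.1% | 79.9% | 79.4% (90:118) |
| 188 | 76.0% | 75.8% | 75.2% (81:107) |

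The loss is about 0.2 points on average and 0.7 to 0.8 at the limit.

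**3. Imbalance by department.** Assume that one department supplies half the patients. The SD of the gap in its share between arms is √(0.5 × 0.5 × 2/n) = √(0.5/n).

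- n = 138 per arm: √(0.5/138) = 6.0 percentage points. A gap of 10 or more has probability 9.7%.
- n = 94 per arm: √(0.5/94) = 7.3 percentage points. A gap of 10 or more has probability 17.0%.

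Looking at all three departments at once, for three assumed mixes of the 276 (simulated, 200,000 draws):

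| Assumed mix | Some department split 60:40 or worse | Some department's share differs by more than 10 points |
|---|---|---|
| 92/92/92 | 13% | 19% |
| 138/83/55 | 26% | 17% |
| 180/60/36 | 37% | 11% |

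**4. What such a gap does to the estimate.** If a department with half the patients explains a share R² of the variance, and the other two are treated as one group, its mean differs from theirs by 2 × 18 × √R². A 10-point gap moves the unadjusted difference by one tenth of that: 0.5, 0.8 or 1.1 points for R² of 2%, 5% or 10%. The target difference is 7, and the standard error at 94 per arm is 18 × √(2/94) = 2.6.

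**5. Gain from adjusting.** Replace SD 18 by 18 × √(1 − R²), with R² assumed.

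| R² | n per arm for 80% power | Power at 104 per arm | Power at 94 per arm |
|---|---|---|---|
| 0 | 104 | 80.1% | 76.0% |
| 2% | 102 | 80.9% | 76.8% |
| 5% | 99 | 82.0% | 78.1% |
| 10% | 94 | 84.0% | 80.2% |

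The gain is 0.8 to 3.9 points at 104 per arm and 0.8 to 4.2 at 94.

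**The case against.** Much of the case for the plan stands. Simple randomisation with probability one half is a valid 1:1 scheme, and nothing in the article requires exactly 138 per arm. A reader might infer from the 4.8% figure that the planned split fails in a way that matters, but step 2 shows that it does not. A reader might also infer that chance imbalance by department biases the trial. It does not: that variation is already inside the t-test's standard error, so the 5% error rate is kept, and the shifts in step 4 are well below one standard error.

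Nor does the article commit to an unadjusted analysis. The tests are given as examples, and a separate analysis plan may name covariates.

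Department is also a coarse proxy. The Introduction's hip fracture and knee arthroplasty examples both fall within orthopaedics, and the third department pools very different operations. No figure in the article says how much variance department explains, so the gain could be near zero.

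Finally, blocking has its own cost here. The first author sends the links, so knows past assignments and could anticipate some later ones near the end of a block. Complete randomisation does not have that weakness.

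What these points leave untouched is that the allocation method is fixed in the article, that it ignores a factor known for every patient, and that using this factor is cheap.

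**Conclusion.** The point holds as a modest improvement, not as an error that undermines the trial. Allocation is unrestricted across three dissimilar departments, and no department term is named in the analysis. The document does not support the readings that the comparison is invalid, that unequal arms matter materially, or that a known amount of precision is being thrown away.

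The likely benefit of adjustment is about 1 to 4 power points, on the assumption that department explains 2% to 10% of the outcome variance. The chance of a gap of at least 10 percentage points in the share of a department supplying half the patients (assumed) is about 10% at randomisation and 17% among completers. These small amounts still count, because at the planned recruitment and drop-out power is about 76%, which leaves no margin.

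**What to change.** **Analysis.** Name as the primary analysis of the physical scale a linear model with treatment group and department, in place of the plain t-test. The cost is one model term (two degrees of freedom).

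**Allocation, preferably.** Replace complete randomisation with permuted blocks stratified by the three departments, with block sizes undisclosed and randomly varying. Someone who does not obtain consent should generate and hold the list, because the first author now both consents and allocates. The cost is three lists instead of one and some predictability at block ends. That predictability is greater here than usual because the first author sees past assignments through the video links; varying the block sizes reduces it but does not remove it.

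**If the list cannot be held elsewhere,** keep complete randomisation and adjust for department in the model only.

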### Participants and recruitment strategy

Surgical patients over 65 years of age will be eligible to participate in the study if they meet the following criteria:They are inpatients.Their home address is one of the municipalities affiliated with the selected hospital.They live at home and are due to return home after discharge directly from hospital or after a short-term training stay at a training centre before returning home.They can read and understand Norwegian.They have consent competence.They have a mobile phone or PC/tablet able to connect to the Internet.They have a body mass index < 24.

Following guidelines by Helsedirektoratet [54] and using NRS 2002 [55] for nutrient screening, the study will be based on the premise that all bedridden older adults undergo nutrition screening during their hospital stay and therefore have a known BMI. Patients receiving only liquid diets, such as tube feeding or intravenous nutritional support, and terminally ill patients will be excluded from the study.

The first author will have access to the department’s record system and will be responsible for informing and obtaining consent from eligible patients. The first author will enter the data into a spreadsheet and assign the participants to the intervention or control groups after the randomisation has been done. Furthermore, a trained external data collector who is not involved in the project will perform all the measurements.

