### Intervention

Participants in the intervention group will be given access to a 6-min educational video 5 days after discharge from the hospital. This will allow the participants to become settled at home or at a training centre to ensure their receptiveness to the intervention. The educational video will present dietary recommendations from the *Kostholdshåndboken* (English: *The Diet Handbook*) published by Helsedirektoratet [58]. The dietary guidelines recommend that malnourished older adults increase their energy and protein intake and provide examples of how older adults can adapt and integrate the recommendations into their preferences and daily mealtime routines [58]. As the participants in the intervention group will be required to access the educational video via their email or smartphone, the video will be made accessible individually through a link sent out by the first author. Through the video, the participants will be encouraged to watch the video several times, with, for example, their relatives or other health personnel. Since it will not be possible to personalise the intervention to each participant, the video information on food and nutrition is based on the following general principles:The information should be simple and correct, according to Contento and Koch [59]; this means keeping the words simple, since the field of nutrition can be full of technical jargon.The information is presented using the active voice rather than the passive voice, since this makes the text more personal [59].The length of sentences varies but is generally kept short [59]. The text of the education manual has undergone several ‘translations’ and revisions to make it easier for people with different assumptions and needs for information to understand. To prevent confusion among patients and strengthen the study’s criterion validity, we collaborated with a nutritionist who provided daily information to the user group to ensure we used precise words and expressions. Furthermore, the face validity of the educational video was confirmed by two bed-ridden patients in the user group who read the script and gave oral and written feedback on its contents. The intervention patients in the feasibility study did not have problems understanding the content, and significant changes in nutritional intake were observed.

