Methodological quality control is crucial in ensuring the repeatability of results. In this trial, quality control will be strengthened in two ways. First, we have developed rigorous inclusion and exclusion criteria. The data collector in each department will further discuss with the first author which patients can be included in the study. Second, we plan to have the same person perform the measurements at the hospital and 3 months after hospital admission. The research team will test this person on their skillset three times during the data collection period to ensure that the measurements will be taken correctly.

Since all intervention participants will view the same educational video, it is impossible to allow for major individual considerations. Thus, linguistic considerations and nutritional recommendations will be based on a standardised health guide. According to Halse [68], it is challenging to find a good balance when information is being delivered to a large group of individuals with different needs. Our study will focus on older adults, which is not a homogeneous group. Thus, making a video that meets every participant’s needs would be impossible. The educational video is, therefore, based on general guidelines. Using the Norwegian *Kostholdshåndboken* (English: *The Diet Handbook*) to increase each patient’s knowledge will increase the study’s content validity. To ensure that the participants will understand the language and content of the video, the script was first face-validated by two older adults who satisfied the inclusion criteria and second through the feasibility study that led to this trial.

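### One person helps decide inclusion, obtains consent, draws the allocation and assigns the group, and no step separates enrolment from control of the allocation

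*Protocol article*

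**What the plan says.** The protocol article assigns the following steps to the first author.

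- **Inclusion.** The Discussion, describing quality control, says: "The data collector in each department will further discuss with the first author which patients can be included in the study".
- **Consent.** Under Participants and recruitment strategy, the first author can see the department's records and "will be responsible for informing and obtaining consent from eligible patients".
- **Draw.** Under Randomisation: "Complete randomisation will be achieved using the free software program RANDOM.ORG", and then "The first author will use the program to allocate participants to the inclusion group or the control group randomly".
- **Assignment.** Under Participants and recruitment strategy, the first author enters data in a spreadsheet and will "assign the participants to the intervention or control groups after the randomisation has been done".
- **Delivery.** Under Intervention, "the video will be made accessible individually through a link sent out by the first author".

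On blinding, the Randomisation section says: "The study will be blinded to the care providers and data collectors". It extends this to the outcome assessor and the statistician and adds: "A code will be allocated to each patient and not revealed before the analysis has been completed". It also accepts that participants cannot be blinded. The Monitoring section says that no coordinating centre, project management group or data monitoring committee is needed.

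**The concern.** Allocation concealment means that whoever enrols a patient cannot know or influence that patient's group until enrolment is final. The usual safeguard is to keep the sequence away from the recruiter. Here the recruiter is the person who draws it.

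If an allocation is known before a patient is approached or finally registered, or if an unwelcome draw can be run again, patients can be steered towards an arm, even without intent. Random allocation then no longer guarantees comparable groups.

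This trial has few other protections against such a bias. Participants know their group, and the primary outcome is a self-completed quality-of-life questionnaire (RAND 36). The Discussion itself says that the video serves patients who have internet access and the skills to use it, or who have help. Digital ability and motivation are therefore plausible grounds for unconscious steering, and neither is listed among the baseline data.

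**Working it through.** The plan gives no figure on this point, so the check traces each step to the person named for it and to what the text says about its timing.

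| Step | Who | Section | Separated from enrolment? |
|---|---|---|---|
| Discussing who can be included | First author with each department's data collector | Discussion | This is enrolment |
| Information and consent | First author | Participants and recruitment strategy | This is enrolment |
| Random draw | First author | Randomisation | No |
| Group assignment | First author | Participants and recruitment strategy | No |
| Sending the link | First author | Intervention | No; requires knowing the group |
| Outcome measurement | External data collector, blinded | Participants and recruitment strategy; Randomisation | Acts after allocation |
| Analysis | Statistician, blinded | Randomisation | Acts after allocation |

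**Order of events.** The text fixes one relation only: assignment follows randomisation. It does not say that randomisation follows irrevocable enrolment. Three procedures fit the wording.

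1. *The whole list is generated in advance.* The first author would then hold it and could know the next group when approaching a patient. Concealment fails.
2. *One draw per patient after consent, without a log.* The group is unknown at consent, but a draw can be repeated, or the registration reconsidered once the result is seen. Concealment depends on trust alone.
3. *One logged draw per patient, after registration is locked.* Foreknowledge is largely excluded, even though one person does everything.

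Only the third is adequate, and the article states neither the lock nor the log that define it.

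**What complete randomisation contributes.** With 1:1 allocation and no blocks, each draw has probability 1/2 for either arm whatever came before. Knowing all past allocations, as the sender of the links would for those already made, gives no information about the next. Guessing from the pattern is excluded. Seeing a list, or repeating a draw, is not.

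**What the blinding contributes.** The withheld code protects measurement and analysis. It cannot hide the allocation from the person who creates it and acts on it.

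**Workload of a separated procedure.** The Sample size section asks for 138 per group, so 2 × 138 = 276 allocations. Trial status gives 11 months of recruitment, so 276 / 11 ≈ 25 per month.

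**The case against.** The best defence is that faulty concealment is inferred rather than stated. The Randomisation section speaks of allocating participants, which can be read as people already enrolled. The recruitment section mentions consent before assignment. An article may also leave the mechanism to a fuller protocol. Eligibility rests largely on objective criteria such as BMI, address and inpatient status, and complete randomisation removes prediction.

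Much of this stands, and it limits the point. A reader might infer that allocation is shown to be unconcealed. The document does not support that, because the timing and control of the draw are unstated, and no advance list or repeated draw is described. A reader might also infer that the first author alone decides on inclusion, alone developed the video, or personally phones the intervention arm. Inclusion is discussed with the departments' data collectors, the development is described as a team effort, and the Intervention section names no caller.

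It would also be too strong to say that any resulting bias could never be seen or adjusted for. Age, education and home-care need are collected at baseline, all measurements are planned during the hospital stay as well as at follow-up, and refusals are tracked. Imbalance in measured factors can be inspected and partly adjusted for. Imbalance in unmeasured ones, such as motivation, cannot.

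The condensation argument does not dispose of the point. The article does more than omit a detail: it names the recruiter as the person who draws and assigns. A fuller document could add a lock or a log, but could not separate the roles without contradicting this text.

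**Conclusion.** The point holds as a matter of role separation. One person takes part in inclusion, obtains consent, draws, assigns and delivers the link, and no described step fixes enrolment before the allocation can be known or prevents a second draw. Selection bias is possible; it is not demonstrated.

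Its size cannot be estimated from the document. Any figure would rest on an assumed prognostic difference between arms for which the text gives no basis, so none is offered here.

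The conclusion assumes that the article describes the roles as they will be carried out. If an unseen procedure already locks registration before a single logged draw, most of the risk disappears and stating that procedure would largely settle the matter. The change is worth making because it is cheap beforehand, whereas bias through unmeasured factors cannot be repaired after recruitment.

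**What to change.** Amend Participants and recruitment strategy and Randomisation as follows.

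- A named role within the existing team, not involved in recruitment, generates the complete randomisation sequence once before recruitment starts and holds it out of the first author's reach.
- The first author records consent and has the baseline measurements completed under a participant number, and only then requests an allocation.
- The holder releases one allocation per request and logs the time. A released allocation is final, and the participant stays in the trial record under it.

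The sequence should stay unblocked, as now planned. Blocking by department is a separate choice that concealment does not need. It would make later allocations more predictable to a recruiter who learns the earlier ones by sending the links.

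The cost is modest continuing work for the holder, about 276 allocations or some 25 a month, and a short wait for each. The wait delays nothing: baseline measurements are made in hospital, and the link goes out 5 days after discharge. No new staff are needed, and the first author can still send the links.
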